# Community case management of chest indrawing pneumonia in children aged 2 to 59 months by community health workers: study protocol for a multi-country cluster randomized open label non-inferiority trial

**DOI:** 10.18203/2349-3259.ijct20201719

**Published:** 2020

**Keywords:** Children under five years of age, Chest indrawing pneumonia, Enhanced community case management, iCCM, Community level health worker, Amoxicillin, Pulse oximeter

## Abstract

**Background::**

The World Health Organization (WHO) integrated management of childhood illness (IMCI) protocol recommends treatment of chest indrawing in 2–59 months old children with oral amoxicillin by trained health facility workers. Whereas, the WHO/UNICEF integrated community case management (iCCM) protocol recommends referral by community level health workers (CLHWs) to a health facility. This study aims to evaluate whether CLHWs can treat chest indrawing pneumonia effectively and safely.

**Methods::**

This multi-centre cluster randomized controlled open label, non-inferiority trial will be conducted in Bangladesh, Ethiopia, India and Malawi. All sites will use a common protocol with the same study design, participants, intervention, control and outcomes. CLHWs will identify 2–59 months old children with chest indrawing. Study supervisors, trained in the iCCM protocol, will confirm CLHWs’ findings. Pulse oximetry will be used to identify hypoxaemic children. In the intervention group, enrolled children will be treated with oral amoxicillin for 5 days, and in the control group they will be referred to a health facility, after providing first dose of oral amoxicillin. An independent outcome assessor will visit each enrolled child on days 6 and 14 of enrolment, to assess study outcomes.

**Conclusions::**

If CLHWs can effectively and safely treat chest indrawing pneumonia in 2–59 months old children, it will increase access to pneumonia treatment substantially, as in many settings, health facilities and trained health workers are not easily accessible. Moreover, this evidence will contribute towards the review of the current iCCM protocol and its harmonization with the IMCI protocol.

**Trial Registration::**

The trial is registered at AZNCTR International Trial Registry as ACTRN12617000857303.

## INTRODUCTION

Of an estimated 0.8 million pneumonia deaths in children under-five years, majority occur in sub-Saharan Africa and South Asia.^1^ Progress in these regions is slow and the disparity between Africa and the rest of the world has grown.^2,3^ As many as 138 million pneumonia episodes are estimated to occur every year.^4^ Mortality among children with pneumonia varies between 0.1% and 30%, depending upon age, severity of signs, promptness and appropriateness of treatment.^5–8^

The World Health Organization (WHO)/UNICEF integrated Community Case Management (iCCM) protocol recommends that community level health workers (CLHWs) refer all children under five years of age with lower chest indrawing to a referral health facility/hospital.^9^ However, many families do not accept referral advice for a variety of reasons, thus reducing access to treatment.^3,10,11^ Several studies reported effectiveness of oral amoxicillin for chest indrawing pneumonia in 2–59 months old children.^12–16^ WHO revised pneumonia treatment guidelines recommending oral amoxicillin for treatment of chest indrawing pneumonia in 2–59 months old children by trained health workers on outpatient basis.^17^ The 2014 Integrated Management of Childhood Illness (IMCI) chart booklet for health facilities is based on this recommendation, which was not extended to the iCCM protocol for community because of insufficient safety and efficacy evidence.^18^

Access to pneumonia treatment could increase substantially if evidence were generated to show effectiveness and safety of oral amoxicillin for chest indrawing pneumonia in 2–59 months old children treated by CLHWs at community level. Additionally, it could decrease referrals, thereby reducing the load on overburdened hospitals and diminishing treatment costs. The overall goal of this study is to contribute to the evidence base for potential revision of the iCCM protocol and its harmonisation with the IMCI protocol.

### Objectives

The primary objective of this study is to determine and compare treatment failure rates of enhanced iCCM compared with standard iCCM in children aged 2–59 months of age with chest indrawing pneumonia without general danger signs and/or hypoxaemia.

The secondary objective is to evaluate the use of pulse oximetry and oxygen saturation (SpO_2_) as a component of a community-based pneumonia management algorithm; specifically, the feasibility of using pulse oximetry by CLHWs and its acceptability by them and mothers/caregivers of children.

## METHODS

### Study design, setting and participants

We designed a cluster randomized controlled trial (CRCT) to be conducted in two African (Ethiopia and Malawi) and two Asian sites (Bangladesh and India). The key characteristics of sites of this open-label, non-inferiority CRCT are shown in Table 1 and explained elsewhere.^19^

### Participants

Children aged 2–59 months with chest indrawing pneumonia whose parents or caregivers consent for participation will be enrolled in the study. Children will be excluded if they have current history of cough for 14 days or more, diarrhoea for 14 days or more, blood in stools, fever for seven days or more, convulsions, persistent vomiting, oedema of both feet, hypoxaemia (SpO_2_ <90%), are unusually sleepy or unconscious on observation, severely malnourished - mid-upper arm circumference (MUAC) <11.5 cm (for 6 months and above age), or were previously enrolled in study.

### Sample size

If there is truly no difference between the standard iCCM and enhanced iCCM (assuming 10% treatment failure in both groups), with design effect of 1.6 and attrition of 10%, then 1340 children 2–59 months of age with chest indrawing per group are required to be 90% sure that the upper limit of a two-sided 95% confidence interval will exclude a difference in favour of the standard iCCM of >5%. Assuming a pneumonia incidence of 0.25 episodes per child per year, and 15% having chest indrawing pneumonia, 30 cases are expected to be enrolled per cluster over the study period of two years. In order to obtain this number, 90 clusters (45 clusters per group) are required. A parallel trial in young infant up to 2 months with fast breathing pneumonia will be carried out at the same study sites and at the same time, which requires 198 clusters (99 clusters in each arm).^19^ We chose the same number of clusters for this trial of children 2–59 months of age with chest indrawing, even though only 90 clusters (45 in each group) were required.

### Study intervention

In the intervention group, all enrolled children with lower chest indrawing will be treated with 80 mg/kg/day amoxicillin in two equal doses for five days. Oral dispersible amoxicillin 250 mg scored tablets will be used, which will be dissolved in expressed breast milk for exclusively breastfed infants. CLHWs will administer the first dose of amoxicillin DT at the place of enrolment and the remaining doses will be provided to mothers or caregivers for administering at home. Mothers/caregivers will be counselled on dose frequency, duration of therapy and importance of adherence. A summary of intervention is shown in Table 2.

### Control

In the control group, CLHWs will refer all children with chest indrawing pneumonia to the nearest health facility in Malawi and to a higher level health facility in India, Bangladesh and Ethiopia.

### Study outcomes

#### Primary outcomes:

Treatment failure will be defined as death at any time within day 1 to day 14 of enrolment, hospitalized for any reason or with any indication for hospitalization on day 6 of enrolment, persistence of chest indrawing on day 6 of enrolment, development of serious adverse effect (anaphylactic reaction, severe diarrhoea, disseminated and severe rash) due to amoxicillin within day 1 to 5 of enrolment.

Treatment failure will only be assessed and declared by an independent outcome assessor (IOA). Withdrawal of informed consent at any time after admission in the study, as well as hospitalization decided by the family, will be recorded but will not be considered as treatment failure.

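### The hospitalisation item of the primary outcome can count control admissions that only follow the allocated referral, and it conflicts with the exemption for family-decided admission; this may bias the non-inferiority comparison

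*Protocol article*

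**What the plan says.** Under Primary outcomes, the protocol article makes hospitalisation one component of treatment failure: the child is "hospitalized for any reason or with any indication for hospitalization on day 6 of enrolment". The other components are death up to day 14, chest indrawing that persists on day 6, and serious adverse effects of amoxicillin. Only an independent outcome assessor may declare failure.

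The following paragraph takes part of this back. Withdrawal of consent, "as well as hospitalization decided by the family, will be recorded but will not be considered as treatment failure". Neither the component nor the exemption is limited to one arm.

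The Control section sets the comparator: "CLHWs will refer all children with chest indrawing pneumonia to the nearest health facility in Malawi and to a higher level health facility" in the other three countries. Tables 2 and 3 agree and add a first antibiotic dose. Intervention children are treated at home. They are seen by the community health worker on days 2, 4 and 7 and referred if they deteriorate (Follow-up section). Table 3 lists no such follow-up in control clusters.

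**The concern.** In a non-inferiority trial, an outcome component that adds failures unrelated to the child's condition to the control arm uses up margin and makes an inferior strategy easier to pass. This component is open to that. Referral is the control treatment, and nothing in the definition sets apart an admission that merely carries it out. Such a child can have no chest indrawing and no indication for admission on day 6 and still be a failure.

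The exemption has a different problem. It is unconditional, so read literally it also removes a child who became worse and was taken to hospital by the family. It also leaves open whether a control family that accepts a referral has decided the hospitalisation. The assessor must choose between two opposed sentences. The article only promises attempts to keep assessors unaware of allocation, and some visits take place in hospital, so that choice may be made with the arm known.

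**Working it through.** **1. The sentences applied to cases**

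| Child | Hospitalisation component | Family exemption |
|---|---|---|
| Control, accepts referral, admitted, well but still an inpatient on day 6 | Failure (any reason) | Not failure, if accepting counts as a family decision |
| Intervention, worsens, taken to hospital by the family, still an inpatient on day 6 | Failure | Not failure, read literally |
| Control, admitted on referral, discharged and well before day 6 | Not failure if the day 6 condition covers both halves of the phrase; failure if it covers only the second half | As in the first row |
| Control, referred, treated as an outpatient or never attends | Not failure on this item | Not relevant |

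The first three rows have no settled answer. The fourth shows that referral alone is never scored.

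**2. The plan's own figure**

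Inputs from Sample size: "assuming 10% treatment failure in both groups"; a margin set to "exclude a difference in favour of the standard iCCM of >5" percentage points; "90% sure that the upper limit of a two-sided 95% confidence interval" meets it; "with design effect of 1.6 and attrition of 10" per cent.

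- n per arm = (1.960 + 1.282)² × 2 × 0.10 × 0.90 / 0.05² = 757
- 757 × 1.6 = 1211
- 1211 / 0.90 = 1346, or 1211 × 1.10 = about 1333

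Both agree closely with "1340 children 2–59 months of age with chest indrawing per group are required". The sample size is not at fault.

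**3. Sensitivity to non-clinical control failures**

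Effective n per arm = 1340 × 0.9 / 1.6 = 754. With observed failure pT (intervention) and pC (control):

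- SE = √[pT(1 − pT)/754 + pC(1 − pC)/754]
- P(declare non-inferiority) = Φ[(0.05 − (pT − pC))/SE − 1.96]

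At pT = pC = 0.10 this gives 89.9%, the planned power. Now put true clinical failure at the margin, 15% v 10%, and add an **assumed** number of points to control failure:

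| Points added to control | Observed pC | Observed difference | P(non-inferiority) |
|---|---|---|---|
| 0 | 10% | 5 | 2.5% |
| 1 | 11% | 4 | 8.4% |
| 2 | 12% | 3 | 20.5% |
| 3 | 13% | 2 | 38.9% |
| 5 | 15% | 0 | 77.6% |

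Example, 1 point: SE = √[(0.15 × 0.85 + 0.11 × 0.89)/754] = 0.0173; 0.01/0.0173 = 0.58; Φ(0.58 − 1.96) = 8.4%.

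If the share h applies only to control children who would otherwise succeed (pC = 0.10 + 0.90h), then h of 1%, 2% and 5% gives 7.5%, 17.5% and 69.3%. The message is the same.

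**4. Effects that can run the other way**

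Suppose, as an assumption, that the exemption removes 10% of true failures:

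- intervention arm only (13.5% v 10%): 14.6%
- both arms (13.5% v 9%): 4.9%
- control arm only (15% v 9%): 0.5%
- control arm only, together with h = 1% (pC = 0.09 + 0.009 = 9.9%): 2.2%, so no inflation

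Extra detection can also cancel the effect. If the earlier follow-up visits add 1 point to intervention failure and referral-driven admissions add 1 point to control, the observed difference is 16% − 11% = 5 points, and the error rate is back at 2.5%.

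**The case against.** A reader might infer that the definition scores the allocated referral itself as failure. It does not: it scores being hospitalised, or having an indication for it. The control text speaks of referral and never of admission. The Introduction says that WHO guidance has facilities treat chest indrawing with oral amoxicillin as outpatient care, and that many families do not take up referral. Children with danger signs or hypoxaemia are excluded at entry. On the natural reading, the affected group is control children still in hospital on day 6 with no indication and no chest indrawing. That group could be close to empty.

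A reader might also infer that the same event counts in control and not in the intervention arm. The wording is alike in both arms, so any asymmetry comes from the care pathways. Intervention children are also referred on deterioration. Of their follow-up visits, those on days 2 and 4 come before the day 6 assessment, and the admissions they prompt count against the intervention.

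Finally, the exemption can be read as an ordinary exception to a general rule, with the operational detail left to the full protocol.

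The first two arguments stand and limit the claim to a risk. The third stands only in part. How a family decision is recorded may well be left to the full protocol. But the article does state the rule, and as stated it can exempt a child who has deteriorated and gives opposite answers for an accepted referral.

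**Conclusion.** The hospitalisation component is badly fixed as stated. It can count control admissions that reflect only the allocated referral, it conflicts with the unconditional family exemption, and its time window is ambiguous. Because it depends on care pathways that differ by allocation, it may bias the primary comparison, and toward non-inferiority if referral-driven control admissions dominate.

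The stronger conclusion, that the trial is biased toward non-inferiority, is not supported. The article gives no admission rate, the true share could be near zero, and the net direction turns on how assessors class accepted referrals and on how much the intervention visits detect. The rise from 2.5% to about 8% or 21% for 1 or 2 points is an illustration. It rests on an assumed share, the planned sample size, attrition and design effect, true failure of 15% v 10%, and no offsetting effect. It does show that a few children per hundred matter against a 5-point margin, which is reason enough to settle the definition.

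**What to change.** Replace the two sentences with one rule that does not refer to allocation:

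- Failure on this item is a clinical indication for hospitalisation found by the independent outcome assessor on day 6, or an admission within a stated window for documented deterioration after enrolment, whoever decided the admission.
- An admission without such an indication is recorded but is not failure, in either arm.

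This is better than exempting only admissions that carry out the allocated referral. That exemption could apply in one arm alone and would require the assessor to know the allocation.

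Report all admissions by arm and reason. Run two sensitivity analyses of the primary outcome: one with the current definition and one without the hospitalisation item.

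The cost is a short amendment and one reason-for-admission item in data collection. The event rate may be slightly lower than under the current wording. The required sample size as planned does not change.

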### Serious adverse events

In case a child presents with a serious adverse events (SAEs) such as death, anaphylactic reaction, diarrhoea with severe dehydration, disseminated or severe rash from antibiotic/oral amoxicillin, the CLHW will contact the study supervisor and IOA. The IOA will confirm and document the SAE and report to the site’s study coordinator or investigator. All SAEs will be reported to WHO within 48 hours of the occurrence.

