**Control clusters**					
Case identification	Detection of cases	CLHWs	Child with an illness is seen by the CLHW either at their place of work or during routine home visits	Community clinic in Bangladesh, Health Post in Ethiopia, Household in India and Malawi	Clinical assessment
Screening and enrolment	Detection of eligible cases	CLHWs	Child is seen by the CLHW either at their place of work or during routine home visits	Community clinic in Bangladesh, Health Post in Ethiopia, Household in India and Malawi	Clinical assessment, and consent
Confirmation of cases	Validation of eligible cases identified by CLHW	Study Supervisor	An eligible child is identified by a CLHW and supervisor is informed	Community clinic in Bangladesh, Health Post in Ethiopia, Household in India and Malawi	Clinical assessment, and confirmation of CLHWs findings, pulse oximetry
Treatment provision	Refer to a referral facility	CLHWs	After enrolment and consent	First dose given at place of enrolment and refer to a referral facility	Counselling for referral
Follow Up	NA	NA	NA	NA	NA
Supervision	NA	NA	NA	NA	NA
Outcome assessment	Outcome assessment	Independent Outcome Assessor	Days 6, 14 and if patient deteriorated in between	Patients household or a hospital if patient was admitted	Clinical assessment and filling outcome assessment form

NA: Not applicable

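### The adverse-effect component of treatment failure counts only reactions to amoxicillin, so a transient serious reaction to another facility antibiotic is not a failure in control: a small bias against enhanced iCCM

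*Protocol article*

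**What the plan says.** All places are in the protocol article.

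- **Primary outcomes.** Treatment failure has an adverse-effect component, "development of serious adverse effect (anaphylactic reaction, severe diarrhoea, disseminated and severe rash) due to amoxicillin within day 1 to 5 of enrolment". Two other components could catch a drug reaction: "death at any time within day 1 to day 14 of enrolment" and "hospitalized for any reason or with any indication for hospitalization on day 6 of enrolment". The remaining component is chest indrawing that persists on day 6.
- **Treatment by arm (Abstract, Methods; Table 3).** The Abstract fixes the drug and its duration for one arm: "In the intervention group, enrolled children will be treated with oral amoxicillin for 5 days". For the other arm, Table 3, control clusters, has "First dose given at place of enrolment and refer to a referral facility"; the Abstract says that this single dose before referral is oral amoxicillin.
- **Control.** Children go to the nearest health facility in Malawi and to a higher-level facility in the other three countries. No antibiotic is named for the treatment given there.
- **Background, Introduction, and Follow-up and assessment of adherence.** The facility guideline for this condition is described as oral amoxicillin. Adherence is defined by oral amoxicillin doses and is to be assessed in control in the same way.
- **Serious adverse events.** The reporting list has a wider attribution, "disseminated or severe rash from antibiotic/oral amoxicillin".

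**The concern.** The trial compares two strategies, and harm from the antibiotic given after referral belongs to the standard strategy. The adverse-effect component is tied to one drug, and which drug a child takes after day 1 depends on the arm. In the intervention arm the component covers every protocol dose. In control it covers only the amoxicillin part of care.

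A component defined this way can miss events in control that it would count in the intervention arm. That lowers the observed control failure rate, moves the estimated difference against enhanced iCCM and costs some power. At stake are a slightly distorted estimate and, at the extreme, a missed demonstration of non-inferiority.

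**Working it through.** **1. Which reactions escape.** Take a listed serious reaction on days 1 to 5.

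| Cause and course | Failure? | By which component |
|---|---|---|
| Amoxicillin, either arm | Yes | Adverse effect |
| Other antibiotic, fatal by day 14 | Yes | Death |
| Other antibiotic, in hospital or with an indication for it on day 6 | Yes | Hospitalisation |
| Other antibiotic, non-fatal, no reason for hospitalisation on day 6 | No, unless chest indrawing persists | None |

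Only the last row is a gap. It arises mainly in control, because the intervention regimen is amoxicillin.

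**2. The plan's own sample size.** Inputs from the Sample size section: failure 10% in both groups, margin 5 points, two-sided 95% confidence interval, power 90%, design effect 1.6, attrition 10%.

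- n = (1.960 + 1.282)² × (0.1 × 0.9 + 0.1 × 0.9) / 0.05² = 10.507 × 0.18 / 0.0025 = 756.5, so 757 per group.
- 757 × 1.6 = 1211; 1211 / 0.9 = 1346 (or 1211 × 1.10, about 1333, if attrition is added instead).
- The stated 1340 is reproduced. No sample-size figure is in error.

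**3. Effective size.**

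- As calculated: 1340 × 0.9 = 1206 evaluable; 1206 / 1.6 = 754 per arm.
- As the trial is to be run: the section adopts the 99 clusters per arm of the parallel trial. At its own 30 cases per cluster, 99 × 30 = 2970; 2970 × 0.9 / 1.6 = 1671 per arm. The cluster size is unchanged, so the design effect of 1.6 is kept.

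**4. Size of the shift.** Let r be the share of control children whose reaction is missed. The article gives no rate, so r is assumed. If listed reactions occur in 0.1% to 1% of control children and 30% to 100% of those reactions are to another antibiotic (both assumed), r runs from 0.1% × 30% = 0.03% to 1% × 100% = 1%. This treats every such reaction as missed, so by step 1 it is an upper bound for any given pair of assumptions.

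**5. Power.** With true failure 10% in both arms, observed control failure is 10% − r and intervention stays at 10%:

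SE = √{[(0.1 − r)(0.9 + r) + 0.1 × 0.9] / n}, power = Φ[(0.05 − r) / SE − 1.96].

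Example at r = 0.5% and n = 754: SE = 0.01528; 0.045 / 0.01528 = 2.945; Φ(0.985) = 83.8%.

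| r (points) | Control children missed, of 1206 | Power, 1340 per arm | Power, 2970 per arm |
|---|---|---|---|
| 0 | 0 | 89.9% | 99.8% |
| 0.03 | 0.4 | 89.6% | 99.8% |
| 0.5 | 6 | 83.8% | 99.2% |
| 1 | 12 | 75.5% | 97.6% |

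**6. False claims.** At a true difference of 5 points and 1340 per arm, the chance of wrongly concluding non-inferiority is 2.5% with no shift, 1.2% at r = 0.5% and 0.5% at r = 1%. It falls as r rises.

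**The case against.** The case against rests on four arguments.

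- **Control children may largely stay on amoxicillin.** The first dose is amoxicillin, the cited facility guideline is oral amoxicillin, and control adherence is to be assessed in the same manner as in the intervention arm. This stands. A reader might infer that control children are exposed to amoxicillin for little more than one dose; the article does not support that. Equally, it does not fix the facility antibiotic, so the gap is not closed.
- **Severe reactions are caught elsewhere.** This stands in part. A reader might infer that any control child who reacts to a facility antibiotic counts as a success. That is wrong, because death by day 14 and hospitalisation or an indication for it on day 6 still count. What remains is the non-fatal reaction that has settled by day 6.
- **Power is hardly touched.** This stands if 99 clusters per arm each enrol 30 children and enrolment is not stopped at 1340; the article states no cap. The distortion of the estimate remains, but it is small.
- **The serious adverse events section is not a rival outcome definition.** This stands. A reader might take "disseminated or severe rash from antibiotic/oral amoxicillin" and "disseminated and severe rash) due to amoxicillin within day 1 to 5 of enrolment" as two contradictory outcome definitions. The former belongs to a reporting list given as examples, which may be broader than an efficacy component. Aligning the wording is a convenience, since the independent outcome assessor both confirms these events and declares failure.

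**Conclusion.** The point holds in a narrow form and is of low importance. The adverse-effect component is not defined alike for the two arms, and nothing else in the article corrects this. The affected events are listed reactions on days 1 to 5 to a non-amoxicillin antibiotic that are non-fatal and give no reason for hospitalisation on day 6.

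The difference shifts against enhanced iCCM by r points on a 5-point margin, with r assumed between 0.03 and 1. The upper end needs reactions in 1% of control children, all to another antibiotic and all missed, which sits badly with the indications that some continue amoxicillin. At 1340 per arm the power cost runs from negligible to about 14 points (89.9% to 75.5%). At 2970 per arm it is at most about 2 points (99.8% to 97.6%).

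A reader might fear that the wording could make an inferior strategy look non-inferior. It cannot: missed control failures work against that claim. The stated sample size is also unaffected.

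**What to change.** In the primary outcome definition, replace the attribution to amoxicillin by attribution to any antibiotic given for the episode, for both arms and over the same day 1 to 5 window. Use the same terms for these reactions in the serious adverse events section, where the wording for rash and diarrhoea now differs from the outcome definition.

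The cost is a few words in the definition and on the outcome and serious adverse event forms. Independent outcome assessors already see both arms and document these events, so no visit or staff is added. The sample size does not change, because the 10% failure assumption is for the composite.
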